**Methods/design:**

This study follows the ‘cohort multiple randomized controlled trial’ (cmRCT) design: rectal cancer patients are included in a prospective cohort that registers clinical baseline, follow-up, survival and QoL data. At enrollment, patients are asked consent to offer them experimental interventions in the future. Eligible patients—histologically confirmed LARC (T3NxM0 <1 mm from mesorectal fascia, T4NxM0 or TxN2M0) located ≤10 cm from the anorectal transition who provided consent for experimental intervention offers—form a subcohort (*n* = 120). From this subcohort, a random sample is offered the boost prior to sCRT (*n* = 60), which they may accept or refuse. Informed consent is signed only after acceptance of the boost. Non-selected patients in the subcohort (*n* = 60) undergo sCRT alone and are not notified that they participate in the control arm until the trial is completed.

sCRT consists of 50Gy (25 × 2Gy) with concomitant capecitabine. The boost (without chemotherapy) is given prior to sCRT and consists of 15 Gy (5 × 3Gy) delivered to the gross tumor volume (GTV). The primary endpoint is pCR (TRG 1). Secondary endpoints include acute grade 3–4 toxicity, good pathologic response (TRG 1-2), clinical response, surgical complications, QoL and (disease-free) survival. Data is analyzed by intention to treat.

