### Secondary endpoints

Secondary endpoints include non-complete pathologic responses (TRG 2–5), acute grade 3–4 toxicity, clinical response, surgical complications, QoL and disease-free and overall survival. The non-complete pathologic responses are categorized as good (TRG 1–2) or ‘not good’ (TRG 3–5) by the pathologist. A radiation oncologist will assess toxicity at weekly visits during the radiation treatment, as well as 4 weeks and 4 months after completion of sCRT. Toxicity is recorded according to the National Cancer Institute’s Common Terminology Criteria for Adverse Events, version 4.03 [26]. Long-term toxicity, (serious) adverse events (SAEs), hospitalization and other health-related problems are registered within the context of the PICNIC cohort during clinical follow-up and annual patient-administered questionnaires on health and oncological status. Clinical response evaluation is based on MRI (9 weeks after completion of chemoradiation; that is, the week before surgery) and DRE and rectoscopy, which are both performed right before surgery while the patient is under anesthesia. MRI and DRE are standardly performed in all patients, whereas rectoscopy is only performed in intervention arm patients who showed a good response based on MRI. For the MRI, a combination of T2-weighted and DWI sequences is used to measure residual tumor tissue in the initially delineated tumor region and its surrounding elective radiation field. Surgical complications are registered up to 30 days after the primary surgery in all patients and after closure of the diverting stoma in patients who previously underwent a LAR. For safety reasons, occurrence of anastomotic leakage is monitored closely in the LAR subgroup by daily review of postoperative patient charts for 30 days. QoL data are recorded by means of either online forms (Patient-Reported Outcomes Following Initial treatment and Long-term Evaluation of Survivorship (PROFILES): http://www.profilesregistry.nl/) or pencil-and-paper questionnaires. For this purpose, cancer-specific QoL questionnaires from the European Organization for Research and Treatment of Cancer (EORTC) are used, including the core (QLQ-C30 [27]) and colorectal cancer-specific (QLQ-CR29 [28,29]) questionnaires. The EORTC QLQ-C30 covers five functional scales, three symptom scales, a global QoL scale and six single items. The EORTC QLQ-CR29 assesses urinary, bowel and/or stoma, psychological and sexually related QoL issues, as well as side effects due to chemotherapy. These questionnaires are provided at the time of diagnosis (baseline) and 3, 6, 12, 18 and 24 months thereafter. Survival and disease-free survival are monitored within the PICNIC project through clinical follow-up records and via a link with the Dutch Cancer Registry. Disease-free survival is defined as the time in absence of a rectal cancer local recurrence or metastasis.

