
### Safety

According to Dutch law, the investigator reports SAEs within 15 days following notification through a government-based internet portal (Centrale Commissie Mensgebonden Onderzoek (Central Committee on Research Involving Human Subjects): https://www.toetsingonline.nl/) to the accredited institutional review board (IRB) that approved the protocol. SAEs that result in death or are life-threatening will be reported within 7 days.

Because this is an exploratory dose escalation study, an independent data and safety monitoring board (DSMB) will make recommendations on continuation of the study based on safety results, focusing on toxicity and anastomotic leakage. The DSMB consists of an expert surgeon, a radiation oncologist and a statistician and is provided, annually or after every SAE, with the raw data on the primary and secondary outcomes (including toxicity, surgical complications and survival). After the first 10 patients with LAR have undergone boost treatment, inclusion of patients scheduled for LAR will be stopped for 8 months to let the DSMB compare anastomotic leakages between boost and control arms. The 8-month period will consist of the time between sCRT to primary surgery (10–12 weeks) followed by the time between primary surgery and bowel reconstruction, including a postoperative monitoring period (16–20 weeks). Only inclusion of patients undergoing LAR will be halted during this stop, because patients undergoing APR have no risk of anastomotic leakage, owing to their permanent stoma. The DSMB analyzes the data independently of the investigators and reports their advice on continuation of the study to the sponsor, which will decide on continuation or stopping of the study.

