### Data analysis

Data will be analyzed according to the intention-to-treat principle. Data of eligible patients who were randomly offered the boost (intervention arm) will be compared with eligible patients who were not randomly selected (control arm). In case of dropout (that is, no surgery following chemoradiation), a worst-case analysis will be performed in which all non-resected intervention-arm patients are classified as non-complete responders and all non-resected control patients are classified as complete responders. However, because omission of surgery is not common practice in our institution, we expect these numbers to be small. In case of substantial boost treatment refusal in the intervention arm, complier average causal effect analysis will be performed to deal with differences in compliance with treatment between both arms [31]. Outcomes include tumor pCR rate (TRG 1), good pathological response (TRG 1–2), clinical response, grade 3–4 toxicity, QoL, recurrence rates and disease-free and overall survival.

The primary outcome (proportion of patients with pCR) will be presented in proportions and compared by means of the χ^2^ test. Toxicity will be presented as the overall and/or time point-specific incidence of grade 3–4 toxicity, and differences will be tested with the χ^2^ test. QoL will be compared at multiple points in time. A relevant change in the patient’s perspective is indicated by a 10% difference or more than 0.5 of the standard deviation [32]. QoL data will be analyzed by mixed-effects models. Differences in disease-free and overall survival rates will be analyzed by Kaplan-Meier analysis and log-rank test. Differences with a *P*-value <0.05 are considered statistically significant, except for the primary endpoint, where *P* < 0.15 has been prespecified.

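### The tested toxicity outcome stops at grade 4, so a toxic death with no separately recorded grade 3–4 event would count as a non-event

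*Protocol article*

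**What the plan says.** Three places in the protocol article give grades for the toxicity outcome, and all three use the same closed range.

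- Abstract, Methods/design: "Secondary endpoints include acute grade 3–4 toxicity, good pathologic response (TRG 1-2".
- Secondary endpoints: "Secondary endpoints include non-complete pathologic responses (TRG 2–5), acute grade 3–4 toxicity, clinical response, surgical complications, QoL".
- Data analysis: "Toxicity will be presented as the overall and/or time point-specific incidence of grade 3–4 toxicity, and differences will be tested" with the χ² test, at the 0.05 level that applies to everything except the primary endpoint. The list of outcomes in that section has the same range.

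The grading scale is the "Common Terminology Criteria for Adverse Events, version 4.03" (Secondary endpoints). The analysis set is also fixed: "Data will be analyzed according to the intention-to-treat principle" (Data analysis). The Safety section expects that deaths may occur: "SAEs that result in death or are life-threatening will be reported within 7 days". No section refers to grade 3 or higher, mentions grade 5, or says how a death from toxicity is scored in the compared incidence.

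**The concern.** A severe-toxicity outcome should include the most severe toxicity. On the named scale a fatal event is grade 5. The article does not spell that out, so it is taken here as a property of the scale that the trial adopts. A range that ends at 4 then leaves the fatal event out of the numerator, and the patient is scored like someone who had no severe toxicity, unless a separate grade 3–4 event was also recorded.

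This matters because the Discussion asks whether the boost can raise the pCR rate safely, and Sample size considerations presents the trial as preparation for studies of still higher doses. The toxicity comparison is part of the evidence for that step. Because the article states the range and repeats it, an analysis plan that follows the article would inherit the gap. The point is therefore a stated rule that needs correction, and not detail left to a later document.

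**Working it through.** **1. The plan's own figure.** The only sample size stated is 60 per arm, for pCR. Inputs from Sample size considerations: 13% pCR in controls, 30% after the boost, 20% refusal, one-sided α of 0.15, power 0.80.

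- Intervention-arm rate after refusal: 0.8 × 0.30 + 0.2 × 0.13 = 0.266. Difference d = 0.136, mean rate 0.198.
- n = [z(0.85)·√(2·0.198·0.802) + z(0.80)·√(0.13·0.87 + 0.266·0.734)]² / d²
- n = [1.036 × 0.5636 + 0.842 × 0.5553]² / 0.0185 ≈ 59.8, so 60 per arm. Power at 60 per arm is 0.801.

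The figure reproduces. It contains no toxicity input, so redefining the toxicity outcome cannot change it.

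**2. How a fatal case is scored under the text as written.**

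- Fatal toxicity, with a separate grade 3–4 event recorded: numerator +1, denominator +1. Counted correctly.
- Fatal toxicity, no separate grade 3–4 event recorded: numerator 0, denominator +1. Not counted.

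Only the second row is a problem.

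**3. Size.** If k patients in an arm of 60 fall in the second row, that arm's incidence is understated by k/60: 1.7 percentage points for k = 1, 3.3 for k = 2. The between-arm difference shifts by (k in boost − k in control)/60, so equal numbers in both arms would leave it unchanged. The documents give neither an expected toxicity rate nor a fatal-toxicity rate, so k cannot be estimated from them.

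**4. Effect on the test, on assumed counts only** (60 per arm, Pearson χ² without continuity correction, uncounted deaths in the boost arm only).

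- 17 vs 9: χ² = 120 × (17·51 − 43·9)² / (26·94·60·60) = 3.14, p = 0.076. Counting one more boost patient, 18 vs 9: χ² = 120 × (18·51 − 42·9)² / (27·93·60·60) = 3.87, p = 0.049.
- 12 vs 9: p = 0.47. Counting one, two or three more boost patients: p = 0.35, 0.25, 0.17.

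The first pair was chosen to sit next to 0.05 and shows only that one patient can matter. In the second series the conclusion does not change.

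**5. Does another planned analysis put the death back into the comparison?**

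- Expedited reporting and the board's data (Safety) serve monitoring and do not feed the χ² table.
- Overall survival (Data analysis) counts deaths from all causes and does not separate toxic from cancer deaths.
- Disease-free survival (Secondary endpoints) is defined by local recurrence or metastasis, so as worded a toxic death is not an event there.
- The worst-case rule for patients without surgery (Data analysis) concerns complete response and has no counterpart for toxicity.

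**The case against.** The strongest reply is that this is a corner case in a secondary endpoint of an exploratory trial, and that safety decisions do not rest on this χ² test. Much of that stands.

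- **Capture is wide.** Toxicity is assessed weekly during radiation, then at 4 weeks and 4 months after chemoradiation. The article also describes blood tests every 2 weeks, registration of serious adverse events and hospitalizations in follow-up, 30-day registration of surgical complications, and daily chart review for leakage after low anterior resection. Many fatal cases would therefore already carry a grade 3–4 entry.
- **Deaths are seen.** They are reported within 7 days, the monitoring board receives raw toxicity, complication and survival data annually or after every serious adverse event, and overall survival is compared by arm.
- **Part of the handling belongs elsewhere.** Worst grade per patient, the time point to which a death is assigned, and denominators at later visits are commonly left to the full protocol or analysis plan, so their absence from an article is no finding.

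These points limit how often the gap would bite. They do not change how the stated range scores the remaining patient.

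A reader might also infer that every mention of toxicity in the article stops at grade 4. It does not: the Background, the Safety section and the Discussion refer to toxicity without a grade limit. The restriction appears wherever a grade is given, which includes the tested outcome.

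**Conclusion.** The point holds as a minor correction. Where the article grades the toxicity outcome, it limits it to grades 3–4. Read literally, a patient who dies of toxicity with no separately recorded grade 3–4 event is a non-event in the between-arm comparison. Each such patient understates that arm's incidence by 1.7 percentage points. This assumes 60 patients per arm, that the deceased stay in the denominator under intention to treat, and that fatal events are grade 5 on the named scale. The number of such patients is unknown and probably small.

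Three stronger conclusions are not supported:

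- That every toxic death costs 1.7 points. Those with an earlier grade 3–4 entry are already counted.
- That a toxic death improves an arm's toxicity rate. The patient stays in the denominator as a non-event, so the rate is understated and does not benefit from the death.
- That toxic deaths are hidden from the trial. They reach the review board, the monitoring board and the survival analysis. They are missing only from the toxicity comparison.

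The sample size and the primary analysis are unaffected.

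**What to change.** In the Abstract, in Secondary endpoints and in Data analysis (both the outcome list and the sentence on testing), replace grade 3–4 with grade 3 or higher (grades 3–5). A death from toxicity in the acute window then counts as an event in the overall incidence. The cost is wording only: fatal serious adverse events are already reported, so no new data, visits or patients are needed.

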### Sample size considerations

On the basis of our center’s experience, we assume that 13% of patients will reach pCR if undergoing sCRT. On the basis of a prediction model published by Appelt *et al.* [30], we expect the pCR rate to be 30% after 65 Gy treatment. Because we consider this study to constitute preliminary work for subsequent studies aimed at evaluating even higher dose increases, we deem it important to find an effect if there really is one, but less important to unjustly find an effect. Therefore, we will use a one-sided α of 15% because it is unlikely that the pCR rate after boost treatment plus sCRT will be lower than after sCRT alone, in combination with a power of 80% because we do not want to increase uncertainty when a negative result is achieved. We further expect that approximately 80% of the patients who receive a boost offer will accept it. Patients who are offered the boost treatment but refuse to undergo the boost will remain in the intervention arm for analysis but receive sCRT (Figure 1). We expect no cross-over from the control arm to the intervention arm, because only patients who are randomly selected to receive a boost offer are informed about and offered it, whereas all non-selected patients undergo standard treatment (that is, sCRT) without receiving information about the boost trial. Taking into account the estimated response rates, together with a 20% refusal rate in the intervention arm, we require 60 patients per arm to demonstrate a statistically significant difference. We expect to complete recruitment within 3 years.

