## Discussion

The RECTAL BOOST study aims to quantify the effect of an external beam radiation (EBR) boost of 15 Gy prior to standard chemoradiation (50 Gy) on pCR rates in patients with locally advanced rectal cancer. Toxicity, clinical (complete) response, (surgical) complications, (disease-free) survival, QoL and feasibility of boost delivery are secondary endpoints. In this study, we will assess in a randomized fashion whether a preoperative 65 Gy EBR-only regimen (15 Gy boost followed by 50 Gy chemoradiation) can safely increase the proportion of patients with pCR (TRG 1) in comparison with the proportion observed after 50 Gy chemoradiation alone. Although contact X-ray [34], brachytherapy, EBR and EBR-brachytherapy combined studies [6] have shown response, sphincter-saving and organ preservation benefits at doses up to 60 Gy, such benefits have not been shown for the 65 Gy dose level when reached by an EBR-only approach.

High rates of good responders are important, as this will increase the number of patients eligible for organ-preserving treatment strategies. These strategies aim to improve the QoL of patients with a good response while their good oncologic outcome, and possible survival benefits, are maintained. Nevertheless, the value of tumor regression has not yet been confirmed as a surrogate endpoint for oncologic outcome in this setting. In the present study, however, all patients, including those with a good clinical response to preoperative treatment, will still undergo surgery because pathological response is the primary endpoint, and because resection remains the standard care according to Dutch guidelines [19]. Therefore, future randomized studies in patients with good clinical responses after (boost) chemoradiation are needed to further assess the effect of radical surgery versus organ preservation on QoL, toxicity and (disease-free) survival. In this study, we aim to quantify response rate by its current gold standard (that is, pathology), which in turn can be correlated to the clinical response data that are also obtained. In so doing, this study will provide important insight into the results of dose escalation that would otherwise be lacking in a trial that would combine dose escalation and omission of surgery within the same trial.

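### The plan asks whether 65 Gy can raise pCR safely, but its only numerical criterion for toxicity is a difference test in a trial sized on pCR alone, and a non-significant result from it cannot support that word

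*Protocol article*

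**What the plan says.** The Discussion of the protocol article puts safety into the trial's question: whether the regimen "can safely increase the proportion of patients with pCR (TRG 1) in comparison with the proportion observed after 50 Gy chemoradiation alone".

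The Data analysis section fixes how toxicity is compared: "Toxicity will be presented as the overall and/or time point-specific incidence of grade 3–4 toxicity, and differences will be tested with the χ^2^ test". The significance level comes from the general rule at the end of that section: "Differences with a *P*-value <0.05 are considered statistically significant, except for the primary endpoint, where *P* < 0.15 has been prespecified". Sidedness is not stated for toxicity, but a χ² test is two-sided by construction.

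The Sample size considerations section derives the trial size from pCR rates and expected refusal and concludes "we require 60 patients per arm to demonstrate a statistically significant difference". Toxicity does not enter. The same section describes the trial as groundwork for testing still higher doses.

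The Safety section adds an independent DSMB that focuses on toxicity and anastomotic leakage, and a pause in LAR inclusion "to let the DSMB compare anastomotic leakages between boost and control arms". These provisions govern whether the study continues. No numerical boundary is attached to them.

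**The concern.** A difference test answers whether the arms can be told apart. It does not say how large an excess of severe toxicity remains compatible with the data, which is what a statement about safety needs. If the test has low power against an important excess, a non-significant result is likely whether or not that excess exists.

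A plausible final report would show pCR significant at the prespecified 15% level and toxicity not significant at 5%. A reader who took this as showing a safe dose could carry a false reassurance into the next escalation, which the protocol already has in view.

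**Working it through.** **Inputs from the protocol article.** 60 per arm, 1:1 allocation; 80% of offered patients accept the boost; refusers stay in the intervention arm (intention to treat); χ² test at 0.05. For reproducing the sample size: pCR 13% vs 30%, one-sided α 15%, power 80%.

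**Input not in the documents.** The control rate *p* of grade 3–4 toxicity. It is assumed, and shown from 5 to 30%.

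**1. Reproduce the plan's own figure.** The intervention-arm pCR rate with 20% refusal is 0.8 × 0.30 + 0.2 × 0.13 = 0.266. The mean of 0.13 and 0.266 is 0.198. With pooled variance under the null and no continuity correction:

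n = [1.036 × √(2 × 0.198 × 0.802) + 0.842 × √(0.13 × 0.87 + 0.266 × 0.734)]² / (0.266 − 0.13)²
= (1.036 × 0.5636 + 0.842 × 0.5553)² / 0.0185 = 1.0514² / 0.0185 ≈ 59.8, so 60 per arm.

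The stated size is therefore fully explained by pCR and refusal.

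**2. Power of the toxicity test against a doubling among boosted patients.** With 80% uptake, and refusers at the control rate, the intervention-arm rate is 0.8 × 2*p* + 0.2 × *p* = 1.8*p*. With full uptake it is 2*p*.

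Worked case by normal approximation, *p* = 10%, intervention arm 18%:
- SE under the null: √(2 × 0.14 × 0.86 / 60) = 0.0634
- SE under the alternative: √((0.10 × 0.90 + 0.18 × 0.82) / 60) = 0.0629
- Power: Φ((0.08 − 1.96 × 0.0634) / 0.0629) = Φ(−0.70) = 0.24, so the miss rate is 76%.

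Exact enumeration over all pairs of binomial counts, with the uncorrected χ² test at 0.05 and 60 vs 60, gives 77% for the same case. The exact miss rates are:

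| Assumed control rate | 80% uptake | Full uptake |
|---|---|---|
| 5% | 87% | 83% |
| 10% | 77% | 67% |
| 15% | 63% | 49% |
| 20% | 49% | 32% |
| 25% | 36% | 18% |
| 30% | 23% | 8% |

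With Yates' correction the 80%-uptake column becomes 94, 83, 72, 58, 44 and 29%.

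**3. What a non-significant result would leave open.** Take 17/60 with the boost offer and 9/60 in controls.
- Difference: 28.3% − 15.0% = 13.3 points
- Pooled rate: 26/120 = 0.217
- z = 0.1333 / √(0.217 × 0.783 × 2/60) = 1.77, P = 0.076
- Wilson limits: 18.5–40.8% and 8.1–26.1%
- Newcombe 95% limits: lower 0.133 − √((0.283 − 0.185)² + (0.261 − 0.150)²) = −0.015; upper 0.133 + √((0.408 − 0.283)² + (0.150 − 0.081)²) = 0.276

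Under the stated rule this is no significant difference, yet the interval runs from about −2 to +28 points. Even identical counts of 6/60 in both arms leave an upper 95% limit of +11.5 points by the same method.

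**The case against.** Toxicity is a secondary endpoint in a trial that calls itself exploratory, and limited power for a secondary endpoint in 120 patients is unremarkable. The protocol promises to present incidences as well as a test. The word *safely* occurs in one sentence of the Discussion, and margins or interval estimates may sit in a fuller document. The miss rates depend on a control rate that nobody has stated. All of this is fair. It makes the point one of interpretation, not of arithmetic. It does not remove the mismatch between a question that the article states and a criterion that the article also states.

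A reader might infer more than the documents support:

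- **That the χ² test is the only safety provision.** It is not. The DSMB receives raw data annually or after every SAE, and there is the LAR pause. The test is the only *numerical* criterion for toxicity.
- **That the protocol will treat P ≥ 0.05 as proof of safety.** No section says so.
- **That the plan contradicts itself by relaxing α for benefit but not for harm.** The reasoning that "we deem it important to find an effect if there really is one, but less important to unjustly find an effect" is given for the primary endpoint. A conventional 5% for secondary endpoints conflicts with nothing, and a looser level for harm would be a preference.
- **That the leakage comparison at the LAR pause is an underpowered difference test.** The Safety section names no test and no number of controls, so there is no stated procedure to criticise.
- **That a one-sided 85% upper bound, matching the efficacy α, would be the natural safety limit.** It lies below the upper limit of the two-sided 95% interval (+5.8 against +11.5 points for 6/60 vs 6/60) and would understate the excess not excluded.

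**Conclusion.** The point holds as a mismatch between question and criterion. The trial undertakes to say whether 65 Gy raises pCR safely, and the stated toxicity test cannot support that word when it is non-significant.

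The size depends on the assumed control rate. With the planned uptake, a doubling of grade 3–4 toxicity among boosted patients is missed in roughly half to nearly nine-tenths of trials at control rates of 5–20%. At 25–30% the miss rate is about a quarter to a third, and with full uptake it is lower throughout. The calculation also assumes that refusers have the control rate and that all 60 per arm are evaluable for toxicity. It is worth correcting because the remedy is cheap and the result is meant to inform further escalation.

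**What to change.** In the Data analysis section, keep the χ² test and add wording such as:

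> For grade 3–4 toxicity, the risk difference (intervention minus control, intention to treat) will be reported with its two-sided 95% confidence interval. A non-significant difference will not be interpreted as evidence of safety. Safety will be described by the upper 95% limit of the excess.

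In the Discussion, either tie *safely* to that limit, or restrict the claim to pCR and describe toxicity as estimated.

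The change needs no extra patients, visits or data. Its one drawback is that the safety statement becomes less favourable, because with 60 per arm the interval will be wide.

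### The sample size uses a one-sided α of 15%, but the primary χ² test at P < 0.15 states no direction; with the usual two-sided χ² P-value, power is about 67%, not 80%

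*Protocol article*

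**What the plan says.** Under Sample size considerations, the protocol article fixes the error rates with a directional argument: "we will use a one-sided α of 15% because it is unlikely that the pCR rate after boost treatment plus sCRT will be lower" (the comparator being standard chemoradiation). The stated power is 80%. The assumed rates are given there too: "we assume that 13% of patients will reach pCR if undergoing sCRT" and "we expect the pCR rate to be 30% after 65 Gy treatment". It expects that "approximately 80% of the patients who receive a boost offer will accept it", and it keeps those who refuse in the intervention arm for analysis. The result is 60 patients per arm.

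Under Data analysis, a χ² test is named in the sentence that begins "The primary outcome (proportion of patients with pCR) will be presented in proportions and compared by means of the". The section closes with a general significance level of P < 0.05, "except for the primary endpoint, where *P* < 0.15 has been prespecified". It does not mention a one-sided P-value, halving of the χ² P-value, a signed statistic, or the direction of the difference.

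**The concern.** For a 2×2 table the Pearson χ² statistic is the square of the two-sample Z statistic for proportions. Squaring removes the sign, so the P-value that software prints is two-sided. Comparing it with 0.15 requires |Z| > 1.44, whereas the sample size rests on Z > 1.04 in favour of the boost. The closing sentence of the analysis section also covers the secondary comparisons, including a χ² test for toxicity, and for the primary endpoint it changes only the number. A reader could easily take it as the same kind of P-value at another cut-off.

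The consequence runs against the authors' stated priority. They accept a higher risk of a false positive so as not to miss a real effect. The stricter rule does the reverse: it halves the nominal false-positive rate in favour of the boost and raises the chance of missing the assumed effect from about 20% to about 33%. Results in the gap between the two rules could also be called either way after the data are seen.

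**Working it through.** **Inputs** (Sample size considerations): control pCR 13%; pCR with boost 30%; 80% acceptance; no cross-over from control; one-sided α 0.15; power 0.80; 60 per arm. The 1:1 allocation is under Random selection.

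**Step 1. Intention-to-treat rate in the boost arm.** Refusers receive standard treatment and stay in the arm:
0.8 × 0.30 + 0.2 × 0.13 = 0.266. The difference is 0.266 − 0.13 = 0.136.

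**Step 2. Reproduce the plan's figure.** Pooled-variance formula without continuity correction:

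n = [z_α √(2p̄(1−p̄)) + z_β √(p₁(1−p₁) + p₂(1−p₂))]² / (p₂ − p₁)²

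- p̄ = (0.13 + 0.266)/2 = 0.198, so √(2 × 0.198 × 0.802) = 0.5636.
- √(0.13 × 0.87 + 0.266 × 0.734) = 0.5553.
- One-sided 0.15: z_α = 1.036, z_β = 0.842. n = [(0.584 + 0.467)/0.136]² = 59.8, so 60 per arm. This matches the plan.

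**Step 3. Same formula with the two-sided χ² P-value at 0.15.** z_α = 1.440, so n = [(0.811 + 0.467)/0.136]² = 88.4, so 89 per arm.

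**Step 4. Power at 60 per arm.** Power = Φ{[0.136 × √60 − z_α × 0.5636] / 0.5553}, with 0.136 × √60 = 1.053.

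| Rule | z_α | Power, formula | Power, exact binomial enumeration |
|---|---|---|---|
| One-sided P < 0.15 | 1.036 | 80.1% | 80.7% |
| χ² P < 0.15, two-sided | 1.440 | 66.9% | 67.6% (favouring boost) |

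Under the design assumptions, 80.7 − 67.6 = 13.1% of trials would be significant under the first rule and not under the second.

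**Step 5. False positives in favour of the boost.** Nominally 15% one-sided and 0.15/2 = 7.5% with the two-sided P-value. Exact enumeration with 13% in both arms gives 15.4% and 7.9%.

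**Step 6. What this looks like in data.** With 8/60 control responders:

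| Boost responders | One-sided P | χ² P |
|---|---|---|
| 13 | 0.115 | 0.230 |
| 14 | 0.078 | 0.157 |
| 15 | 0.052 | 0.104 |

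For 14: Z = 0.100 / √(0.1833 × 0.8167 × 2/60) = 0.100/0.0706 = 1.42. The one-sided rule is met from 13 responders and the two-sided rule from 15.

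**Sensitivity.** The article does not say whether a continuity correction applies. With Yates' correction, exact power is 73.9% one-sided and 59.6% two-sided, so the gap remains.

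**The case against.** The strongest reply is that the analysis section never says two-sided. It calls the 0.15 threshold prespecified, and the only 15% level given before it is the one-sided α, which comes with a directional rationale. A χ² test on a 2×2 table can be reported one-sided, by its signed root or by halving P in the expected direction. On that reading power is about 80% and the defect is a missing word. This stands as a limit on the claim: 67% is what follows if the usual χ² P-value is used, not an established property of the trial. It does not remove the point, because the named test and threshold, applied in the ordinary way, give a different rule from the one the trial was sized for.

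A second reply is that this is a condensed article about an exploratory trial, and such detail belongs in the full protocol or analysis plan. That would hold if the article were silent, but it names both the test and the cut-off. It is fair, however, that the two-sided reading errs towards fewer false claims of benefit; its cost is lost sensitivity.

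Three stronger readings are tempting and are not supported:

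- A reader might infer that 60 per arm can only come from a one-sided test. That is true for the refusal-diluted rates. A two-sided 15% test on the undiluted 13% versus 30% also gives 59.8, so 60 per arm. It conflicts with the one-sided α and the refusal allowance that the article states, so it does not reconcile the two sections.
- A reader might infer that a difference favouring control would count as a positive result. The article says only that such a difference would be statistically significant, and the Discussion asks whether the boost can increase pCR. Under the design assumptions that outcome has a probability of about 0.04%.
- A reader might infer that this test decides whether higher doses are studied. The article calls the trial preliminary work for later studies and sets no go/no-go rule.

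**Conclusion.** The point holds conditionally. The sample size section is one-sided and internally consistent (60 per arm, power about 80%), while the analysis section names an undirected χ² test at the same 0.15. If the usual two-sided P-value is used, power falls by about 13 percentage points to about 67%, and 80% power would need 89 per arm. These figures assume 13% versus 26.6% pCR and no continuity correction. If the 0.15 was meant as one-sided, power is as stated and the wording alone needs repair. Either way the rule should be settled before the arms are compared, since a plausible result such as 8/60 versus 14/60 changes its conclusion with the reading.

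**What to change.** In the Data analysis section, or in the analysis plan with a reference from it, state the primary rule in one sentence. For example: pCR will be compared with a one-sided test of two proportions (the signed square root of the Pearson χ² statistic, without continuity correction), significant if one-sided P < 0.15 in favour of the boost arm; this is equivalent to χ² P < 0.30 with the observed difference favouring the boost.

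This restores the rule the trial was sized for. It costs one sentence and no additional patients.

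If a two-sided test at 0.15 is really intended, keep the test, say that it is two-sided, and correct the sample size section to a power of about 67% at 60 per arm (or 89 per arm for 80%).

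Reporting the risk difference with a one-sided 85% lower bound and a two-sided 95% confidence interval would help readers but is optional.
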